#### Research objective

##### Main objective

To determine whether the ANI-loop medical device reduces the total amount of remifentanil (remi) administered compared with standard practice.

##### Secondary objectives and hypotheses

To determine whether the automated administration of remifentanil by the ANI-loop device allows:

- improving hemodynamic stability during propofol general anesthesia.
- increasing the time spent with an ANI between 50 and 70.
- reducing immediate post-operative pain.

In the *"ANI-loop*" arm only: determine whether ANI-loop enables fully automated administration (i.e. without the need to disengage the device).

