##### Calculating the number of subjects

The aim of the study was to assess whether the ANI-loop medical device could reduce the total amount of remifentanil (remi) administered compared with standard practice. Based on literature data [Leal PC et al.] and the department's usual practice, the total amount of remifentanil in the control group can be estimated at 0.30 ± 0.075 (mean ± standard deviation). To demonstrate a 20% reduction in the *ANI-loop* arm (i.e., a mean remifentanil quantity of 0.24 in the experimental group), with a first-species risk of 5% and a power of 80%, we need to include 26 patients per group, for a total of 52 patients.

Reference:Leal PC, Sakata RK, Salomão R, Sadatsune EJ, Issy AM. Braz J Anesthesiol. 2013 Mar- Apr;63(2):178-82.

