- propofol target adapted in both arms to maintain the hypnotic component index (BIS® or Entropy®) in the range [40-60]. During *the procedure*, propofol target changes will be made 1 minute after the last target change has become effective, and will follow the indications in table 1. This corresponds to the usual management in the burn unit of the Burn Treatment Center.

|  |  |  |
| --- | --- | --- |
| component  hypnotic | propofol target |  |
| >80 | + 2.0 |  |
| >60 | + 1.0 |  |
| <40 | - 0.5 |  |
| <25 | - 1.0 |  |
| **Table 1: Adaptation of propofol targets in both arms** | | |

|  |  |  |
| --- | --- | --- |
| ANI | target remi |  |
| <35 | + 2.0 |  |
| <50 | + 1.0 |  |
| >70 | - 0.5 |  |
| >90 | - 1.0 |  |
| **Table 2: Adaptation of remi targets in the "standard practice" arm** | | |

- remifentanil target
  - **in the *standard practice* arm**: increased to 4 ng.ml-1 at the start of *the procedure*, then adjusted to maintain ANI in the range [50-70] as indicated in Table 2. Target changes are made 1 minute after the last target change has become effective. This corresponds to usual management at the Burn Treatment Center.
  - **in the *ANI-loop* arm**, the automatic mode of the ANI-loop device is engaged at the start of *the procedure*. The flow of remifentanil is automatically regulated by the ANI-loop. The anaesthetist can switch to manual mode at any time in the event of inadequate regulation (device disengagement). The device is switched off at the end of the *procedure.*

Pre-emptive analgesia

- local infiltration of skin sample area with naropein 2 mg.ml-1 during

*intervention*

- paracetamol 1g IVL at end of *procedure*
- sufentanil 0.12 µg.kg-1 (max 10 µg) IVL at *end of procedure*

Prevention of postoperative nausea/vomiting

- ondansetron 4 mg IVL

Postoperative analgesia

- morphine titration according to Visual Analogue Scale (VAS), bolus of 3mg every 3 min (max 12mg)
- ketamine 20 mg IVL for persistent pain with VAS ≥ 40

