Since 2008, the Physiodoloris® monitor has been used in the orthopedic surgery unit of the Lille University hospital. We observed and recorded ANI evolution and reactions on more than 2000 patients during orthopedic surgical procedure under general anesthesia. Thanks to this experience, we determined several decision rules based on ANI_i_ and ANI_a_ analysis in order to help anesthesiologists understand ANI guided anesthesia. In order to regulate analgesic drug administration, we determined two types of action:

- ***Infusion flow Changes:*** Increase or decrease the syringe pump infusion rate.
- ***Bolus:*** Infusion rate fast increase during 10 s. Infusion rate returns to its previous value after these 10s.

Each action is followed by a *refractory period* which shuts down the regulation algorithm for several seconds.

Several regulation variables and constants are defined.

*Variables used for regulation:*

- ***ANI_i_ :*** instantaneous ANI.
- ***ANI_a_ :*** average ANI.
- ***S_i_*** : ANI_i_ slope (computed on 30 s).
- ***S_a_*** : ANI_a_ slope (computed on 30 s).
- ***InF:*** Syringe pump infusion Flow (in µg/Kg/min).

*Constants used for regulation (set by the user):*

- ***ANI_max_*** : representing the ANI max value.
- ***ANI_min_*** : representing the ANI min value.
- ***S_a_*** T: representing the S_a_ threshold
- ***S_i_*** T: representing the S_i_ threshold
- ***InI:*** Infusion Rate increment (in µg/Kg/min).
- ***InF_min_*** : Minimum infusion rate (in µg/Kg/min).
- ***Inf_max_*** : Maximum infusion rate (in µg/Kg/min).
- ***BolusI:*** Infusion Flow bolus increment (in µg/Kg/min).
- ***RefP****:* Refractory period (in s)

***ANI_mean_*** is computed as

ANI_mean_ = ANI_min_ +(ANI_max_ -ANI_min_ )/2 (2)

The defined rules are established in order to treat both acute pain and global analgesia level changes.

*Acute pain treatment:*

**If**(ANI_i_ < ANI_min_ **)and(**S_i_ <-S_i_ T)**then** Bolus (3) Bolus corresponds to an Infusion rate increase of *Bolus* µg/Kg/min during 10 s.

Infusion rate returns to its previous baseline after these 10s.

Each Bolus is followed by a 3*RefP refractory period.

*Analgesia level changes:*

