#### ANI_min_ <ANIa< ANI_max_ :

In this area, we consider that analgesia in adequate. However, in order to anticipate, we consider the ANI_a_ slope (S_a_ ) changes in order to regulate the infusion rate.

**If**(ANI_a_ <ANI_mean_ **)and**(S_a_ <-S_a_ T)**and**(InF+InI<InF )_max_

**then** InF = InF+ InI (5)

**If**(ANI_a_ > ANI_mean_ **)and** (S_a_ >S_a_ T)**and**(InF- InI>InF )_min_

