#### ANIa>75 :

**then** InF = InF- InI (6)

In certain condition, we consider that if ANI is too high, ANS doesn't respond to noxious stimuli. This effect could be explained by an opioid overdose which would require an infusion flow decrease.

**If**(S_a_ >0)**and**(InF- InI>InF_min_ **)then** InF = InF- InI (7) Each infusion rate change is followed by a RefP refractory period.

In order to avoid arterial hypotension (SBP<80 mmHg), we added two rules on systolic blood pressure (SBP).

**If** SBP<90 **then** InF = InFmin (8)

**If** SBP<80 **then** InF = 0 (9)

In the case of SBP<80 mmHg, the regulation algorithm is shut down until SBP recovers a value over 85 mmHg. Rules (8) and (9) have the highest level of priority.

*C - Algorithm implementation*

From a technical point of view, the system consists in a software ("controller") implemented on a classical personal computer allowing to adapt in real time the syringe pump infusion rate according to ANI_i_ and ANI_a_ evolutions. ANI_i_ and ANI_a_ values are obtained from the Physiodoloris monitor communication interface and SBP is obtained from the Anesthesia monitor (Datex Ohmeda AS-5, GE Healthcare or

Intelliview® Philips^TM^ ). The syringe pump (Alaris GH, Cardinal health) and the two monitors are linked to the computer through a Keyspan® 4-port serial to USB adapter.

The software also allows users to enter patient characteristics (age, size, weight, ASA) and constants values used for regulation. Thanks to the interactive aspect of the controller, all the predefined constants can be adapted and manually changed during the regulation. Finally, a specific software interface allows users to follow the variable's evolution, the syringe pump status and the regulation results. Direct syringe pump commands are also available in order to allow the anesthesiologists to manually adapt the syringe pump infusion flow or to shut down the automatic regulation.

Constants used for regulation are defined as follow:

- ***ANI =75_max_***
- ***ANI =50_min_***
- ***S T=7_a_***
- ***S T=25_i_***
- ***InI=0.01 µg/kg/min***
- ***InF_min_ =0.05 µg/kg/min***
- ***Inf_max_ =0.6 µg/kg/min***
- ***BolusI= 0.04 µg/kg/min***
- ***RefP=10 s***

Blood pressure is measured every 2.5 minutes.

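### The ANI objective scores 50–70, the range the control arm is titrated to, but the loop is specified for 50–75, so the result cannot separate quality of control from a different set range

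*Protocol*

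**What the plan says.** **Objective and criterion.** The Protocol, under Secondary objectives and hypotheses, asks whether automation succeeds in "increasing the time spent with an ANI between 50 and 70". Evaluation criteria then splits intervention time, for instantaneous and mean ANI, into below 50, 50–70 and above 70. The synopsis repeats both.

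**Control arm.** Under Practical aspects of the research (anesthesia procedure, maintenance), the remifentanil target is raised at the start of the procedure and "then adjusted to maintain ANI in the range [50-70] as indicated in Table 2". Table 2 lowers the target once ANI exceeds 70, with no condition on trend.

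**ANI-loop arm.** The main text says only that the device regulates the flow, so the rules come from Appendix I. Its constants are ANImin = 50 and ANImax = 75. Of the zone between them it says: "In this area, we consider that analgesia in adequate". Within that zone, rule (6) lowers the flow only when average ANI is above the midpoint and its slope exceeds the threshold of 7. The too-high rule, rule (7), has 75 written into its heading as a number and also needs a positive slope. Appendix I adds that "all the predefined constants can be adapted and manually changed during the regulation", but gives no upper limit other than 75.

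**The concern.** The scored band, the control rule and the objective agree on 70 as the upper limit. Only the tested device works to 75, and the protocol does not explain why. The objective is meant to show whether automation holds patients in range better than manual titration. That reading requires both arms to be aiming at the range that is scored. If the loop arm spends less time in 50–70, the cause may be poorer control or faithful execution of a wider range. If it spends as much or more, the size of the advantage is equally hard to interpret. What is at stake is the conclusion on one secondary objective.

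**Working it through.** **1. The plan's own figure.** No number is planned for the ANI objective. The stated sample size belongs to the primary endpoint: difference 0.30 − 0.24 = 0.06, SD 0.075, standardized difference 0.06/0.075 = 0.8. A two-sided 5% t-test with 80% power needs 25.5, hence 26 per group (power 80.7% at 26). It reproduces and is unaffected by this point.

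**2. The ranges side by side.**

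| Item | Range | Width | Midpoint | At a stable ANI of 70–75 |
|---|---|---|---|---|
| Objective and criterion | 50–70 | 20 | – | scored out of range |
| Control, Table 2 | 50–70 | 20 | 60 | target lowered |
| ANI-loop, Appendix I | 50–75 | 25 | 50 + (75 − 50)/2 = 62.5 | no ANI rule acts |

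The disputed zone is 75 − 70 = 5 points, or 5/25 = 20% of the loop's own band.

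**3. What the loop does in 70–75.** Rule (6) needs average ANI above 62.5 and a slope above 7, so it acts on a steep rise but not on a stable value. Rule (7) does not apply until 75 is passed. So 70–75 is not a complete dead zone, but a steady ANI there is left alone in one arm and acted on in the other.

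**4. Illustration of size.** The documents give no distribution of ANI. Assume that it is normal with the same SD σ in both arms, centred at each band's midpoint (μ = 62.5 loop, 60 control). Time in [a, b] = Φ((b − μ)/σ) − Φ((a − μ)/σ). With σ = 7:

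- Loop, 50–70: Φ(7.5/7) − Φ(−12.5/7) = 0.8580 − 0.0371 = 82.1%.
- Control, 50–70: Φ(10/7) − Φ(−10/7) = 0.9234 − 0.0766 = 84.7%.

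| σ | 50–70, loop vs control | 50–75, loop vs control | Loop time in 70–75 |
|---|---|---|---|
| 5 | 92.7% vs 95.4% | 98.8% vs 97.6% | 6.1% |
| 7 | 82.1% vs 84.7% | 92.6% vs 90.7% | 10.5% |
| 10 | 66.8% vs 68.3% | 78.9% vs 77.5% | 12.1% |
| 15 | 48.9% vs 49.5% | 59.5% vs 58.9% | 10.6% |

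**5. Sensitivity to the assumed centre.** Keep σ = 7 and the loop at 62.5 (82.1% in 50–70), and move only the control centre:

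- 60: control 84.7%, loop lower by 2.6 points.
- 62.5: control 82.1%, no difference.
- 65: Φ(5/7) − Φ(−15/7) = 0.7625 − 0.0161 = 74.6%, loop higher by 7.5 points.

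The sign in step 4 is therefore a product of the assumed centres. What the illustration does show is that the choice of band can change which arm looks better.

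**The case against.** The strongest reply is that no net disadvantage to the device has been shown, and that reply stands. Neither arm steers to a midpoint. Table 2 makes no change between 50 and 70 and uses larger steps up than down; in the loop, the midpoint only gates slope-triggered steps. On a steep rise rule (6) can cut the flow from 62.5 upward, where Table 2 does nothing until 70. The loop can act again after a 10 s refractory period, while control waits 1 minute after the last target change has taken effect. A reader might infer from step 4 that the criterion is biased against the device; step 5 shows that the documents do not support this.

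A reader might also infer that the primary comparison is confounded because the loop tolerates a higher stable ANI. That does not follow. The main objective compares the device, with its algorithm and constants, against standard practice. The arms also differ in infusion mode, boluses, slope rules and blood-pressure cut-offs, so aligning 70 with 75 would not isolate automation, and the protocol does not claim to isolate it.

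Two further replies stand in part. Time above 70 is already reported in both arms, but the bands do not separate 70–75 from higher values. The constants can be changed by the user, but no study value other than 75 is stated. An added tabulation could sit in an analysis plan, which is not shown here. The disagreement between device specification, control rule and criterion lies in the protocol itself.

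**Conclusion.** The inconsistency is in the current text and needs no assumption to establish: 70 in the objective, the criterion and the control rule, against 75 in the only specification of the loop. It covers 20% of the loop's acceptable band. A result on time in 50–70 cannot distinguish quality of control from a different set range. The effect on the estimated difference cannot be derived from the documents in size or direction: the illustration gives 0.6 to about 3 points against the device with midpoint centring, zero or the opposite sign with other centres. The point limits the interpretation of one secondary objective. It does not invalidate the primary comparison or change the sample size.

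**What to change.** Reconcile the objective and criterion (with the synopsis), Table 2 and Appendix I. In Appendix I both places matter: the ANImax constant and the separate rule that has 75 written as a number, since changing the constant alone would leave that rule where it is. Which range applies is a clinical choice for the sponsor and investigators.

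If the ranges are meant to differ, state this and the reason, analyse time in both 50–70 and 50–75 in both arms from the recorded ANI data, and word the conclusion on the ANI objective to say that the arms worked to different ranges.

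The second route costs one extra tabulation and a sentence in the report. The first may need a protocol amendment, because it changes either a device setting or a control rule that the protocol describes as the unit's usual management.

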#### Research design

##### Experimental design

- category 1 randomized controlled trial versus standard practice
- monocentric: Lille university hospital burn treatment center. Randomization carried out by the data management division directly via the electronic CRF
- in the *"ANI-loop"* arm, autonomous administration of remifentanil by the ANI- loop medical device under the supervision of an anesthetist
- in the "standard practice" arm, administration of remifentanil adapted by the anaesthetist according to usual practice
- ANI monitor visible on both arms

##### Definition of the study population

The ANI measurement provided by the PhyioDoloris monitor cannot be interpreted in several situations. All the criteria concerned are taken into account in the non-inclusion or exclusion criteria;

- arrhythmia
  - Exclusion criteria
- absence of breathing (e.g. apnea due to intubation)
  - Not applicable; the ANI-loop device is not used in automatic mode when the patient is not intubated and mechanically ventilated.
- respiratory rate below 9 cycles/min
  - Not applicable; the protocol provides for a respiratory rate of 12 minute cycles.
- current volume variable over the measurement time, i.e. 64 seconds
  - Not relevant; for this type of anaesthesia, tidal volume adjustments are usually made at most 1 to 2 times per hour. Significant changes in

tidal volume over a period of 64 seconds are not used in this clinical context.

- irregular breathing (when talking, laughing or coughing)
  - Not applicable; the ANI-loop device is not used in automatic mode when the patient is not intubated and mechanically ventilated.
- pace maker (certain types)
  - Non-inclusion criteria
- heart transplantation
  - Non-inclusion criteria
- Use of drugs affecting cardiac sinus activity (Atropine...)
  - Excusion criteria; atropine injections(parasympatholytic) andpropranolol (sympatholytic)
    1. Inclusion criteria
- patients treated at the Lille CHRU Burn Treatment Centre
- burn surgery: excision-grafting
- age ≥ 18 years
- informed consent
- ASA I or II or III status
- general anaesthesia with intubation and controlled assisted ventilation
- body mass index between 17 and 40 kg.m-2
  - 1. Non-inclusion criteria
- pregnant or breast-feeding women (simple questioning)
- pace maker (regardless of operating mode)
- heart transplantation
- non-sinus rhythm
- dysautonomia
- diabetes mellitus with micro or macro angiopathic complications
- foreseeable allergy or intolerance to a drug used in the study
- baseline" hemodynamic measurements considered as hypotension or bradycardia
- FCbl>120 min^-1^ or PASbl>160 mmHg
- uninsured
- persons deprived of their liberty, in emergency situations, or persons incapable of consent and not benefiting from a legal protection regime (guardianship/curatorship)
- unconscious or sedated patient before induction

NB: There is no pregnancy test to check this criterion; it will be a simple questioning.

- - 1. Exclusion criteria
- Arrhythmia
- significant extrasystole (more than two extrasystoles per minute without interruption during surgery)
- Intraoperative atropine injection
- Intraoperative injection of propranolol.

If a patient is excluded, his or her inclusion is deemed null and void; the investigating center will then proceed with an additional inclusion in replacement. No follow-up of the excluded patient is justified by participation in the study.

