##### Analysis method and strategy

Statistical analyses will be carried out using SAS software (version 9.4 or higher) at the Lille CHRU's methodological support platform, under the responsibility of [name]. All statistical tests will be two-sided, with a first-species risk of 5%. No intermediate analyses are planned. A detailed statistical analysis plan will be drawn up and validated before the database is frozen.

Patient characteristics at inclusion will be described for each of the two study arms. Qualitative variables will be described by numbers and percentages. Quantitative variables will be described by the mean and standard deviation in the case of a Gaussian distribution, or by the median and interquartile range (i.e. 25th and 75th percentiles) in the opposite case. The normality of distributions will be tested by a Shapiro-Wilk test and verified graphically by histograms.

Primary objective: The total amount of remifentanil administered (value related to weight and duration of intervention) will be compared between the two arms of the study by a Student's t-test; the effect size will be calculated (standardized mean difference) with a 95% confidence interval. If the distribution of the primary endpoint deviates from normality, the Mann-Whitney U test will be used.

Secondary objectives: Qualitative secondary endpoints will be compared between the two arms of the study using a Chi-square test or Fisher's exact test (when the validity conditions of the Chi-square test are not met). Quantitative secondary endpoints are compared between the two arms of the study using a Student's t-test, or a Mann-Whitney U-test if the distribution of the endpoint deviates from normality. Quantitative secondary endpoints measured at different times will be compared between the two arms of the study using a linear mixed model. This model takes into account the correlation between repeated measurements in the same patient, and the possible existence of missing data. The choice of correlation model will be based on the AIC criterion. The validity of the model will be studied by analyzing the residuals. In the event of significant deviations from normality without obvious transformation of the criterion, the criteria will be compared at each time point between the groups using Mann-Whitney U tests. Finally, secondary criteria identified only in the

The "*ANI-loop*" model will be described using the usual descriptive statistics.

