##### Practical aspects of the research

- - 1. Informed consent

It will be obtained after information during the pre-anaesthetic consultation or during the final pre-anaesthetic visit, by one of the investigator(s). The patient will receive the information form and will be asked to sign the consent form in triplicate, after a reasonable period of reflection.

- - 1. Devices used for anesthesia

General anesthesia is induced and maintained by propofol and remifentanil.

- Propofol is administered in both arms by an intravenous anesthesia system with a pK/pD concentration target: Primea Orchestra® base (Fresenius) used routinely in the department.
- Remifentanil is administered
  - in the "*standard practice"* arm, by an intravenous anesthesia system with a concentration target based on a pK/pD model: Primea Orchestra® base (Fresenius) used routinely in the department. Authorized targets according to standard practice range from 0.0 to 10.0 ng.ml^-1^ during anesthesia.
  - In the *ANI-loop* arm, remifentanil is automatically administered by the ANI-loop medical device.
    1. Anesthesia procedure

*Welcoming patients to the operating room*

Installation of standard monitoring equipment

ECG, plethysmography, non-invasive blood pressure (NIBP), entropy, ANI.

Collection of usual hemodynamic constants and calculation of HR thresholds_bl_ and PAS_bl_ used in intra-anaesthesia.

Randomization directly via electronic CRF and allocation to *"standard practice"* or *"ANI-loop"* arm.

The Physiodoloris® monitor (ANI index) remains visible in both study arms.

*Induction of anesthesia*

Similar anesthetic induction in both groups: midazolam 0.08 mg.kg^-1^ IVD

remifentanil target set at 8.0 ng.ml^-1^

propofol target set at 5.0 µg.ml^-1^ then increased in 1 µg.ml increments^-1^ until loss of consciousness.

Tracheal intubation, possibly after curarization

propofol and remifentanil targets lowered to 3 µg.ml^-1^ and 3 ng.ml respectively^-1^

Controlled Assisted Ventilation (CAV): tidal volume of 8 ml.kg^-1^ of ideal weight, ventilatory frequency: 12 cycles.min^-1^

Tidal volume will be adapted to maintain FetCO2 in the range [30 - 35 mmHg].

*Maintenance of anesthesia during the procedure*

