##### Criteria for discontinuing study participation

Each subject may leave the study by decision of the competent administrative authority, the sponsor and the principal investigator, but also by decision of an investigator or by decision of the subject him/herself, in accordance with the regulations and as mentioned in the consent form.

- the presence of a major extrasystole (more than two extrasystoles per minute without interruption) is a criterion for stopping a patient's participation in the study, because ANI measurements are not possible under these conditions.
- In this case, the patient's inclusion would be deemed null and void; the investigating center would then proceed with an additional inclusion in replacement.
- no follow-up of the excluded patient is justified by participation in the study.

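### Randomised patients who have an intraoperative exclusion event are voided, replaced and not followed, so the arms compared are no longer the randomised arms

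*Protocol*

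**What the plan says.** Under the anaesthesia procedure (Practical aspects of the research), allocation is made on arrival in the operating room, before induction: "Randomization directly via electronic CRF and allocation to" one of the two arms.

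The exclusion criteria (Definition of the study population) are arrhythmia, more than two extrasystoles per minute without interruption during surgery, "Intraoperative atropine injection", and intraoperative propranolol. The last three are intraoperative by their wording. Arrhythmia has no stated timing, but non-sinus rhythm is already a non-inclusion criterion, so arrhythmia mainly adds later events.

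The consequence is fixed in the same section: "If a patient is excluded, his or her inclusion is deemed null and void; the investigating center will then proceed with an additional inclusion". It continues: "No follow-up of the excluded patient is justified by participation in the study". The section on discontinuing participation repeats the rule for extrasystoles: "In this case, the patient's inclusion would be deemed null and void". The protocol nowhere keeps these patients in an analysis.

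The reason given is that ANI cannot be interpreted under these conditions. The primary criterion is total remifentanil related to weight and duration of the intervention.

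**The concern.** A randomised comparison is protected only while membership of the arms is settled by the allocation. Here it is settled partly by what happens afterwards.

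Dependence on the arm is plausible for two reasons. First, remifentanil delivery is the randomised variable and follows different rules once the procedure starts: target steps by Table 2 in control; small rate changes, boluses and blood-pressure cut-offs in the loop (Appendix I). The protocol itself lists bradycardia as frequent and asystole as rare with remifentanil. Second, the trial is single-blind and the anaesthetist manages or supervises remifentanil knowing the arm, while two of the four exclusions are drug injections.

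If exclusion is related to dose and differs between arms, the primary estimate is biased in a direction that cannot be predicted. Patients whose ANI became unusable are also likely candidates for leaving automatic mode, so removing them may flatter the disengagement results. A later SAP could change the analysis set but could not recover data that were never collected.

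**Working it through.** **Plan's own figure.** Inputs from the sample-size section: control mean 0.30, SD 0.075, ANI-loop mean 0.24, so a difference of 0.060 (0.8 SD); two-sided 5% (analysis section). The stated result is "a power of 80%, we need to include 26 patients per group, for a total of 52 patients". By noncentral t, with noncentrality 0.060 / (0.075 × √(2/26)) = 2.88 and 50 degrees of freedom, power is 80.7% at 26 per group and 79.1% at 25. The figure reproduces; the point does not rest on a sample-size error.

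**How many patients could be left out.** The exclusion rate is not given. To retain 52 at an assumed rate e, 52/(1 − e) must be randomised: 55, 58, 62 or 65 at 5%, 10%, 15% or 20%. So 3, 6, 10 or 13 randomised patients would be missing from the comparison.

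**Effect on the primary comparison.** Assume a share p of an arm is excluded and that these patients average k SD above the mean of all randomised patients in that arm. The retained mean is then

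μ − p × k × 0.075 / (1 − p).

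For 15% control, 5% ANI-loop and k = +1:

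- control: 0.30 − 0.15 × 0.075 / 0.85 = 0.2868
- ANI-loop: 0.24 − 0.05 × 0.075 / 0.95 = 0.2361
- difference: 0.0507 (0.676 SD), power 67%

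The same formula over a range, with 26 retained per arm and the SD held at 0.075:

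| Control / ANI-loop excluded | k | Difference | Power |
|---|---|---|---|
| any equal rates | any, same in both arms | 0.060 | 81% |
| any rates | 0 | 0.060 | 81% |
| 15% / 5% | +0.25 | 0.058 | 78% |
| 15% / 5% | +0.5 | 0.055 | 74% |
| 10% / 5% | +1 | 0.056 | 75% |
| 15% / 5% | +1 | 0.051 | 67% |
| 15% / 5% | −1 | 0.069 | 90% |
| 5% / 15% | +1 | 0.069 | 90% |

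With no true difference, 5% control and 15% ANI-loop at k = +1 give a spurious reduction of 0.075 × (0.15/0.85 − 0.05/0.95) = 0.0093.

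**Second model.** A simulation of 20,000 trials per scenario let the chance of exclusion rise with the patient's own dose (logistic, slope 1 per SD) and filled each arm to 26 retained. With no true difference, 10% exclusion in both arms gave a type I error of 5.1% and no bias; 5% control against 20% ANI-loop gave 7.8% and a spurious reduction of about 0.010. With the true 0.060, 20% control against 5% ANI-loop gave 0.051 and 70% power. This dependence is milder than k = +1, so a larger imbalance in rates is needed for a similar shift.

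**The case against.** The strongest defence is that the exclusions have a clinical and technical reason that applies to both arms. ANI drives dosing in control (Table 2) as well as in the loop, so when ANI is uninterpretable neither regimen can be delivered as specified. That is a fair reason to analyse such patients separately. It is not a reason to void them. The remifentanil total can be measured without ANI, and the protocol already allows manual mode at any time and counts disengagements as an outcome.

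Induction is similar in both arms, with the same remifentanil target, and automatic mode starts only with the procedure. Events before that point cannot be caused by the difference in regimen. This stands and narrows the exposure window, although the anaesthetist already knows the allocation by then.

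Three stronger readings are tempting and are not supported:

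- A reader might infer that bradycardia cases vanish. Bradycardia is not an exclusion criterion, and episodes not treated with atropine stay in the secondary criterion on haemodynamic time. That atropine would be given for bradycardia is an inference; the protocol mentions atropine as a drug affecting sinus activity.
- A reader might infer that safety data are erased or that replacement conceals the losses. Adverse events are recorded, serious ones are reportable from consent to the end of participation, and without time limit if likely due to the research or device. Inclusions are notified to the sponsor in real time, and deviations are reported with reasons.
- A reader might infer that high-dose patients are the ones who leave. Nothing in the protocol gives that direction.

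**Conclusion.** The point holds as a defect of a stated conduct rule. Events after randomisation, which delivery of the allocated treatment and an unblinded anaesthetist can influence, decide who is compared. Affected patients drop out of the remifentanil, haemodynamic and disengagement results and lose the assessments between extubation and two hours after it (pain, morphine, ketamine, nausea and vomiting).

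The size is illustrative only. It rests on assumed exclusion rates, an assumed dose relation and an unchanged SD. It runs from zero, through a loss of about 0.009 from the planned 0.060 (power about 67%), to an inflation or a spurious effect of the same amount. The documents do not show that bias of any given sign will occur; they show that nothing in the plan prevents it. Because the remedy is simple and the missing data cannot be recovered later, it should be corrected.

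**What to change.** Amend the exclusion and discontinuation sections so that voiding and replacement do not apply to any patient already randomised. Then:

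- analyse all randomised patients in their allocated arm for the primary criterion, with remifentanil recorded to the end of the intervention;
- continue haemodynamic collection and the assessments up to two hours after extubation following such an event;
- restrict only the ANI-derived criteria to time when ANI can be evaluated;
- report the number of exclusion events, by type, in each arm;
- keep the currently restricted set as a sensitivity analysis.

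The planned 26 per group is unchanged, and replacement is no longer needed for the primary criterion. The cost is a short amendment and the post-extubation assessments in the few affected patients, which have to be carried out because they are not pump or monitor data. The estimated effect may be slightly diluted by patients who left automatic mode. Clinical management, including the decision to leave automatic mode, is unaffected.
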